# The ELECLA trial: A multicentre randomised control trial on outcomes of neoadjuvant treatment on locally advanced colon cancer

**DOI:** 10.1111/codi.16908

**Published:** 2024-02-16

**Keywords:** locally advanced colon cancer, neoadyuvant chemotherapy, Survival

## Abstract

**Background:**

Colon cancer (CC) is a public health concern with increasing incidence in younger populations. Treatment for locally advanced CC (LACC) involves oncological surgery and adjuvant chemotherapy (AC) to reduce recurrence and improve overall survival (OS). Neoadjuvant chemotherapy (NAC) is a novel approach for the treatment of LACC, and research is underway to explore its potential benefit in terms of survival. This trial will assess the efficacy of NAC in LACC.

**Methods:**

This is a multicentre randomised, parallel‐group, open label controlled clinical trial. Participants will be selected based on homogenous inclusion criteria and randomly assigned to two treatment groups: NAC, surgery, and AC or surgery followed by AC. The primary aim of this study is to evaluate the 2‐year progression‐free survival (PFS), with secondary outcomes including 5‐year PFS, 2‐ and 5‐year OS, toxicity, radiological and pathological response, morbidity, and mortality.

**Discussion:**

The results of this study will determine whether NAC induces a clinical and histological tumour response in patients with CCLA and if this treatment sequence improves survival without increasing morbidity and mortality.

**Registration number:**

NCT04188158.

What does this paper add to the literature?Neoadjuvant chemotherapy is increasingly tested and employed for the treatment of locally advanced colon cancer. ELECLA trial will assess the impact of this novel approach in terms of survival, safety, feasibility and efficacy. This is a pragmatic trial, which employs an oxaliplatin‐ and fluoropyrimidine‐based scheme for pMMR colon adenocarcinoma.

## INTRODUCTION

Colon cancer (CC) is a public health problem due to its high prevalence and increasing incidence in younger patient populations [1]. It is the leading cause of cancer‐related death among males aged 20–49 years, with an ascending trend in young women in the USA [2].

Based on current clinical practice, the mainstay treatment for locally advanced CC (LACC) (stage III and high‐risk stage II) is oncological surgery followed by adjuvant chemotherapy (AC), which aims to decrease the risk of locoregional and distant relapse and increase overall survival (OS) [3]. Based on previous experiences with other locally advanced gastrointestinal tumours, neoadjuvant chemotherapy (NAC) is a relatively new concept in the treatment of LACC [4, 5, 6].

There are several potential advantages of NAC in LACC, such as reduced tumour cell‐shedding during surgery, increased likelihood of R0 resection, reduced number of positive lymph nodes, control of systemic metastatic spread, and the ability to test tumour chemosensitivity in vivo [7, 8, 9, 10]. Furthermore, the use of NAC is independent of eventual surgical complications, thus avoiding AC delays and improving chemotherapy completion rates.

Theoretically, however, NAC might increase perioperative complications and mortality rates. It has been a concern that tumour growth during NAC, in the case of poor tumour response, could lead to local complications, such as bowel obstruction or perforation requiring emergency surgery or even metastatic disease development. Furthermore, over staging by current imaging methods may lead to the overtreatment of low‐risk patients [8].

Several studies have demonstrated the safety and efficacy of NAC, but a survival benefit is still unclear [11, 12, 13, 14]. NAC has recently been added to the American guidelines from the National Comprehensive Cancer Network (NCCN) as an alternative for selected LACC cases (TNM‐T4b tumours) [15], based on studies that revealed a significantly improved survival rate [7]. Therefore, it is of great interest to explore the potential benefit of neoadjuvant therapy in LACC, analysing whether the tumour's response translates into a survival benefit.

## METHODS

This trial has been registered at ClinicalTrials.gov (https://clinicaltrials.gov/ct2/show/NCT04188158). The protocol has been structured following the Standard Protocol Items: Recommendations for Interventional Trials (SPIRIT) guidelines [16].

### Study objectives

The primary objective of this study is to determine if a therapeutic scheme based on NAC, surgery, and AC (Intervention group) increases the 2‐year progression‐free survival (PFS) compared to the standard treatment, based on surgery followed by AC (Control group) for LACC.

The secondary objectives are as follows:
To determine if the intervention group regimen increases 5‐year PFS compared to the control group.To determine if the intervention group increases 2‐ and 5‐year overall survival (OS) compared to the control group.To compare postoperative morbidity and mortality in both groups.To assess toxicity in both groups.To assess the therapeutic compliance rate in both groups.To assess the accuracy of the CT scan for the diagnosis of LACC in the control group.To assess the accuracy of the CT scan to evaluate tumour response after NAC in the intervention group.To validate the use of tumour response scales in CC.To determine if the addition of oxaliplatin impacts the pathological response in the group of patients over 70 years of age receiving NAC.

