### Study setting

Those responsible for recruiting and selecting patients for inclusion in the research project belong to each centre's Multidisciplinary Committee on Colorectal Cancer. A recruitment period of 2 years is estimated. Toxicity, compliance rate, tumour response, and perioperative morbimortality rate will be assessed. Two‐ and five‐year OS and PFS will be calculated.

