#### Postoperative morbidity and mortality

Postoperative morbidity and mortality will be graded according to the Clavien‐Dindo classification [22]. Transfusion requirements and long‐term outcomes will also be recorded, including incisional hernia and readmission. Chemotherapy toxicity will be recorded according to the CTCAE version 4.0.

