Patient selection and their corresponding therapeutic strategy are determined by CT scan. Several studies suggest that preoperative staging has limited accuracy [38, 39, 40], whereas other support its impact on survival [41, 42]. A significant concern raised from the data collected in these studies is whether preoperative CT staging is accurate enough to avoid overtreatment for low‐risk patients who otherwise would not require NAC or AC. In the preliminary results of the FOxTROT study, only 7% of T2N0 tumours were misclassified [8], although, in the results, 24% of control patients did not meet the criteria for AC [25]. Meanwhile, a Spanish study evaluated the accuracy of CT after NAC, and over staging was observed in 9.1% of cases [43]. In another study published by Huh et al. with more than 500 patients, CT had accuracies of 79.1% and 73.3%, respectively, for T and N staging. Radiological staging was also found to be an independent predictor of long‐term survival and was recommended for selecting patients with CC participating in clinical trials with NAC [42]. Magnetic resonance imaging allows a better soft tissue discrimination and diffusion‐weighted imaging and may become an interesting complementary tool for the selection of patients [44].

Another drawback is the possibility of continued tumour growth despite neoadjuvant treatment. In the FOxTROT trial, 4.3% of patients that received NAC required emergency surgery due to obstruction during preoperative treatment [34]. According to a single‐arm randomised phase II study with 47 patients, none had progression while receiving CapeOX (oxaliplatin plus capecitabine) [45]. Consistent results were observed in another study with 65 LACC patients, with a tumour volume reduction of 62.5%, without any case of progression [14]. In patients that undergo surgery upfront, some factors may encourage the development of micrometastasis and tumour progression, such as the stimulation of growth factors associated with the procedure and immunosuppression during the early postoperative period. In a recent propensity score matching analysis, none of the patients experienced progression, and the incidence of distant recurrence was significantly reduced [46]. NAC could control these potential factors, thereby improving the efficacy of cancer surgery through local downstaging and elimination of circulating tumour cells, potential micrometastases, and lymph node metastases [46, 47].

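### The morbidity and mortality comparison is worded as postoperative, so emergencies and deaths before planned surgery, which fall mainly in the neoadjuvant arm, are outside it

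*Protocol article*

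**What the plan says.** The Discussion paragraph of the abstract states a two-part conclusion: the results are to show whether NAC "improves survival without increasing morbidity and mortality".

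Three places define what is counted for the second part:

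- Study objectives: "To compare postoperative morbidity and mortality in both groups".
- Postoperative morbidity and mortality: "Postoperative morbidity and mortality will be graded according to the" Clavien-Dindo classification. The same paragraph adds "Chemotherapy toxicity will be recorded according to the CTCAE version 4.0".
- Study setting: "Toxicity, compliance rate, tumour response, and perioperative morbimortality rate will be assessed". Here the word is perioperative, and it is not defined.

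The Introduction names the harm that NAC might cause before surgery. Tumour growth during treatment "could lead to local complications, such as bowel obstruction or perforation requiring emergency surgery". The Discussion gives a rate from the cited phase III trial: "4.3% of patients that received NAC required emergency surgery due to obstruction during preoperative treatment".

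Under Statistical analysis and sample size calculation, progression-free survival (PFS) runs from randomisation and includes death, overall survival (OS) runs from surgery, and all randomised patients enter the intention-to-treat analysis. The sample size of 238 rests on 2-year PFS alone.

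**The concern.** The arms reach surgery at different times after randomisation. The control arm has no planned treatment before the operation. The NAC arm has three cycles of chemotherapy and then a waiting interval. A comparison that starts at surgery therefore leaves out a long stretch of follow-up in one arm and a short one in the other.

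The harm the authors worry about happens in that stretch. A patient who obstructs or perforates during NAC has had a serious event that a postoperative count does not record as such. A patient who dies before surgery cannot contribute to postoperative mortality and has no time origin for OS. Both omissions make NAC look safer than it is over the whole treatment course. At stake is the second half of the conclusion the abstract announces.

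**Working it through.** **Inputs from the article.** NAC lasts 9 weeks and surgery follows 4 weeks after its completion (Intervention group). Emergency surgery for obstruction during preoperative treatment: 4.3% (Discussion). Sample size: 119 per arm, including 5% dropout. No complication rate, mortality rate or control-arm time to surgery is given.

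**1. The plan's own figure.** The 119 per arm is for PFS of 75% against 90%. With two-sided 5%, 80% power and continuity correction, n = 113 per arm, and 113 / 0.95 = 118.9, rounded up to 119, or 238 in total. (The text says unilateral alpha; that mismatch is a separate matter.) For safety the useful range is 113 evaluable to 119 randomised per arm.

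**2. Length of the uncounted period in the NAC arm.** 9 + 4 = 13 weeks under XELOX, plus any delay between randomisation and the first dose. The length of the FOLFOX alternative is not given.

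**3. Expected emergencies before planned surgery.** 0.043 x 119 = 5.1 patients, or 0.043 x 113 = 4.9.

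**4. How far this could move the comparison.** Let q be the share of these patients who are counted anyway because they have a complication after the emergency operation. Let c be the rate of similar events in controls before surgery. The excess hidden from the comparison is 4.3 x (1 - q) - c points. Neither q nor c is in the article. With c = 0:

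| q (assumed) | Hidden excess |
|---|---|
| 0 | 4.3 points |
| 0.5 | 2.15 points |
| 1 | 0 |

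Perforations and pre-operative deaths would add to this; the article gives no rate for them.

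**5. Precision of the comparison.** With equal true rates p, the 95% half-width is 1.96 x sqrt(2p(1 - p)/n). The rates p are assumptions.

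| p | n = 119 | n = 113 |
|---|---|---|
| 10% | 7.6 points | 7.8 points |
| 20% | 10.2 | 10.4 |
| 30% | 11.6 | 11.9 |
| 40% | 12.4 | 12.8 |

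For an assumed 2% mortality the half-width is 3.6 to 3.7 points, though the normal approximation is rough with so few deaths (0.02 x 119 = 2.4 per arm).

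**6. What a test could show.** With 113 per arm and a two-sided 5% test, power to detect a true 5-point excess is 20%, 14% and 12% at control rates of 10%, 20% and 30%. Even 5 of 119 against 0 of 119 pre-operative emergencies gives a two-sided Fisher p of 0.060.

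**The case against.** The case on the other side is substantial.

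- A reader might infer that deaths during NAC are lost to the trial. They are not. PFS runs from randomisation, counts every death and is analysed by intention to treat. What stands is narrower: these deaths are missing from postoperative mortality and from OS. PFS merges them with recurrence, so it does not answer the mortality question.
- Toxicity is assessed in both groups with CTCAE, and the Study setting section says perioperative. Some events during NAC may therefore be recorded. But the CTCAE sentence covers chemotherapy toxicity, and obstruction from a growing tumour is not clearly that. The two terms for the surgical outcome are inconsistent and need reconciling.
- Patients who need emergency surgery are operated on, and nothing limits Clavien-Dindo grading to planned operations. The elective-surgery wording is an eligibility criterion, not an analysis set. Their later complications can count against NAC. This shrinks the lean (q above), but the event that forced the operation is still not counted.
- A reader might infer that a non-significant result will be taken as proof of no harm. The article does not say so. It names no test or decision rule for morbidity, only a general 5% level, and an analysis plan that is not shown may use estimation. The precision figures are therefore a caution about wording, not evidence of a planned error.
- Morbidity is a secondary objective in what the Discussion calls a phase II trial, and low precision for such outcomes is usual. That is fair. The starting point of the count is a different matter, because it can be corrected without more patients.

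**Conclusion.** The concern holds in this form: the stated conclusion covers morbidity and mortality in general, while the objective and outcome that support it begin at surgery. As worded, about 5 of 119 NAC patients could have a pre-operative emergency that is not an event in the comparison, a lean of up to about 4 points in favour of NAC. The true size depends on three things the article does not give: whether the cited 4.3% applies here, how many of these patients are counted through later complications, and how often controls have similar events while awaiting surgery. The direction rests on the control arm having no planned treatment, and so little time, before its operation.

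Separately, the trial is too small for a claim of no increase to mean more than its confidence interval allows. Under the assumed complication rates of 10 to 40%, an observed difference of zero would still leave an excess of roughly 8 to 13 points unexcluded.

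**What to change.** Reconcile the Study objectives, Study setting and Postoperative morbidity and mortality sections so that they describe one main comparison:

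- **Population:** all randomised patients, in the arm assigned.
- **Window:** from randomisation to a fixed time after surgery, or to an equivalent stated time for patients never operated on.
- **Events:** complications and deaths, including unplanned surgery, obstruction and perforation before the planned operation.
- **Secondary:** the postoperative Clavien-Dindo comparison, kept as it is.
- **Reporting:** the risk difference with its 95% confidence interval. Word the conclusion as the excess that the upper limit excludes, in place of an unqualified statement of no increase.

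The cost is a change of wording and some extra analysis, with no change to treatment or sample size. The date and nature of events before surgery must be on record. The article does not say that they are, and with more than 100 patients already entered by July 2023, some may have to be taken from hospital notes. The NAC-arm figure may look less favourable than under the postoperative count.

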### Study design

This is a randomised, multicentre, parallel‐group, open label, controlled clinical trial. Both treatment groups can be framed within the usual clinical practice, and the procedures associated with the study do not deviate significantly from it.

### Eligibility criteria

#### Inclusion criteria

Clinical: (1) Histological confirmation of colon adenocarcinoma; (2) Age > 18 years for both males and females; (3) Good performance status (Karnofsky >60%, ECOG <2); (4) Blood analytics: haemoglobin >10 g/dL, leucocytes >3,0 × 10^9^/L, platelets >100.000 × 10^9^/L, glomerular filtration >50 mL/min, and total bilirubin <25 micromol/L; (5) Absence of chemotherapy contraindication and (6) Written and oral informed consent.

Radiological: (1) LACC: T4 or T3 with >5 mm extramural invasion on CT scan; (2) With or without nodal invasion on CT scan; (3) Absence of any distant metastases (M0) and (4) Radiologically resectable disease.

Therapeutical: All patients who undergo elective surgery with curative intention, regardless of the technique: open, laparoscopic, or robotic approach.

#### Exclusion criteria

(1) Significant comorbidity, uncontrolled angina, and myocardial infarction in the last 6 months; (2) Personal history of other neoplasia in the last 5 years; (3) Uncontrolled infective disease; (4) Pregnancy or breastfeeding; (5) Peripheral neuropathy grade > 1; (6) Rectal cancer (<15 cm from the anal verge or below peritoneal reflection); (7) Distant metastases or peritoneal carcinomatosis; (8) Bowel obstruction; (9) Microsatellite instability; (10) Refusal to participate or to give written informed consent and (11) If the patient cannot understand the purpose of the study or comply with its procedures.

### Study setting

Those responsible for recruiting and selecting patients for inclusion in the research project belong to each centre's Multidisciplinary Committee on Colorectal Cancer. A recruitment period of 2 years is estimated. Toxicity, compliance rate, tumour response, and perioperative morbimortality rate will be assessed. Two‐ and five‐year OS and PFS will be calculated.

### Patient identification and consent

All patients are evaluated at the time of diagnosis through medical history, physical examination, complete blood test with tumour markers, colonoscopy with biopsy and analysis of microsatellite instability. The patients are examined using a multidetector CT scan with oral and intravenous contrast. The standard CT acquisition protocol was performed in the venous phase and a section of 1.5 mm width was performed. This same protocol is employed for assessing the response in the interventional arm. In addition, a molecular determination is recommended but not mandatory: K‐N‐RAS and BRAF.

Potential candidates will be informed of the possibility of participating in the study verbally and in writing. Those who agree to participate (with written consent) and pass screening with the inclusion and exclusion criteria will be randomly assigned to one of the following treatment groups: (1) Intervention group: NAC + surgery + AC, or (2) Control group: Surgery + AC.

### Randomisation

Centralised randomisation will be performed with a 1:1 ratio using a computer‐generated sequence. Patients will be randomised either to the interventional or control group after first obtaining their informed consent. Stratified randomisation is performed based on the radiological T and N stages into four groups: T3N‐, T3N+, T4N‐, and T4N+. The attending surgeon will then be informed of the patient's treatment group. When obtaining consent, the attending surgeon will not be aware of the assigned group, as the randomisation will be performed afterwards.

### Interventions

#### Intervention group

NAC will follow a scheme based on three cycles of XELOX (capecitabine 1000 mg/m^2^ days) 1–14 + oxaliplatin 130 mg/m^2^ on day (1) every 21 days, over the course of 9 weeks. Oncological surgery will take place 4 weeks after completing NAC. The XELOX scheme could be replaced by five cycles of FOLFOX, depending on the practice of each centre.

Given the inconclusive data on the addition of oxaliplatin in patients over 70 years old in the MOSAIC [17] and NSABP C‐07 studies [18], in this subgroup of patients or in those with some comorbidities which limit the use of oxaliplatin, such as nephropathy, three cycles of capecitabine alone could be used instead exceptionally.

AC will start 4–6 weeks after surgery based on five cycles of XELOX, according to the initial clinical staging. If this interval is exceeded, the use of complementary therapy is left to the researcher's discretion.

#### Control group

The indication for AC will be based on the pathological findings; it is usually recommended in stage III or high‐risk stage II tumours. The standard scheme is based on eight cycles of XELOX.

According to the investigator's criteria and the usual guideline of each centre, the XELOX scheme could be replaced by 12 cycles of FOLFOX. In patients over 70 years old, eight cycles of capecitabine alone could be used exceptionally.

In this way, several therapeutic options are presented, collected in routine clinical practice, and in accordance with the most recent European, American, and Japanese reference guidelines [19] (Figure 1).

**FIGURE 1 codi16908-fig-0001:**
[figure not shown]
Flow diagram showing each stage of the trial. *Exceptionally in the group of patients with contraindication for oxaliplatin.

### Outcome parameters

The primary outcome of this trial will be 2‐year PFS. Follow‐up will be performed by Oncology and General Surgery Services, as per usual practice. During the first 2 years, a physical examination and assessment of tumour markers will be done every 3 months, whereas a thoracic‐abdominal‐pelvic CT scan will be performed every 6 months. One year after surgery, a colonoscopy will be performed. If no lesions are identified, repeat colonoscopy will be done after 5 years. If polyps are identified, then it will be requested after 2‐years. From the third to fifth postoperative year, physical examination, tumour markers, and CT scan will be performed every 6 months.

### Secondary outcome analysis

#### Tumour response grade

In the intervention group, the tumour response grade assessment will be radiologically assessed 3 weeks after NAC finishing by comparing pre‐ and post‐treatment TNM, tumour volume, and also according to the RECIST criteria [20]. Moreover, the pathological tumour response will be recorded, employing a modified Ryan scale, which is commonly used in rectal cancer [21].

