In locally advanced rectal cancer, the impact of a pathological complete response (PCR) has been assumed to be a predictor of improved outcomes, but this assumption is still debatable for LACC [34]. To address this, Change et al. conducted a prospective observational study of 60 LACC patients who received neoadjuvant treatment and surgery; the PCR rate was higher in T3–T4a versus T4b patients, and PCR significantly improved patient OS [26]. The recent results of the OPTICAL trial, presented at the ASCO 2022 meeting, showed that NAC induced a 7% PCR rate and 20% tumour downstaging rate (pT0‐2N0M0) [35]. Significant tumour regression was also reported in the PRODIGE 22, a French phase II multicentre trial, which randomised 104 LACC patients to curative resection followed by AC or NAC followed by surgery and AC. Patients that underwent neoadjuvant treatment were more likely to achieve tumour remission grades 1–2 (44% vs. 8%, *p* < 0.001) [36]. Moreover, the PCR rate in the FOxTROT trial was 4%, and 62% of patients had some kind of regression. These findings are consistent with the previous published literature [14, 28], but there was no evidence that panitumumab improved the efficacy of NAC in patients with RAS wild‐type tumours [25]. This same trial demonstrated a 5‐year recurrence rate of 30% for those patients with no regression versus 0% in those with PCR, thus highlighting the importance of assessing the correlation between PCR and therapeutic outcomes [25]. These points should be considered when choosing and guiding adjuvant treatment, maybe in combination with the detection of minimal residual disease by circulating tumour DNA [37].

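### Tumour response is planned as an uncontrolled within-arm measure, yet the abstract promises to determine whether NAC induces it

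*Protocol article*

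**What the plan says.** In the Discussion part of its abstract, the article makes a causal promise: "The results of this study will determine whether NAC induces a clinical and histological tumour response". One of the secondary objectives is "To validate the use of tumour response scales in CC".

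The section on tumour response grade assigns the assessment to one arm: "In the intervention group, the tumour response grade assessment will be radiologically assessed 3 weeks after NAC finishing". The radiological measures compare CT before and after treatment on "TNM, tumour volume, and also according to the RECIST criteria". The pathological measure follows in the same paragraph: "Moreover, the pathological tumour response will be recorded, employing a modified Ryan scale, which is commonly used in rectal cancer". That sentence names no arm; its place in the paragraph points to the NAC arm.

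The next section, on correlation between radiological and pathological findings, relates the two kinds of response in the intervention group only. It uses the control group for one purpose, the diagnostic accuracy of baseline CT against pathology. Neither section states a comparison of response between the arms.

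**The concern.** A statement that NAC induces response needs an estimate of what the same measure would show without NAC. Two sources of apparent response need no drug effect.

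- **CT reading error.** Patients enter because CT shows T4, or T3 with more than 5 mm extramural invasion. Selection on a high reading means that a second, equally fallible reading will on average be lower. This affects TNM change. Tumour volume and RECIST do not depend on T/N category error, although they too have no comparator.
- **Background regression grade.** The article itself cites a trial in which some patients operated on without NAC were placed in the responding grades.

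As planned, neither source is separated from the effect of NAC. At stake is a secondary conclusion, the response rate attributed to NAC.

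**Working it through.** The article gives no design figure for response, so there is none to reproduce. The check uses figures quoted in its DISCUSSION.

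**Inputs**
- Regression grade, French randomised phase II trial of 104 patients: "Patients that underwent neoadjuvant treatment were more likely to achieve tumour remission grades 1–2 (44% vs. 8" (the 8 is also a percentage). The scale is not identified as the modified Ryan scale.
- CT accuracy, study of more than 500 patients: 79.1% for T, 73.3% for N; direction of error not given.
- Evaluable patients per arm: 119 × 0.95 ≈ 113, from the sample size section.

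**1. Background regression grade**
- Expected responders without drug effect, if 8% applied: 113 × 0.08 ≈ 9.
- Share of a 44% rate: 8/44 = 18%. Difference between arms: 44 − 8 = 36 points.
- With an assumed background of 2% or 15%, the count is 2.3 or 17 of 113.

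**2. CT against CT, no true change**

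Assumptions: a binary stage (high or lower); two independent reads; sensitivity and specificity both equal to the quoted accuracy *a*; true-high share π from 0.9 down to 0.5.

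P(second read lower | first read high) = a(1 − a) / [πa + (1 − π)(1 − a)]

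| | a(1 − a) | π = 0.9 | π = 0.5 |
|---|---|---|---|
| T, a = 0.791 | 0.1653 | 0.1653/0.7328 = 23% | 0.1653/0.5 = 33% |
| N, a = 0.733 | 0.1957 | 0.1957/0.6864 = 29% | 0.1957/0.5 = 39% |

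These are upper-end figures. Errors shared by both scans, which use the same CT protocol, would cancel in part. The eligibility criteria select on T and admit any N, so the N row applies only to patients read node-positive at baseline; those read negative can move the other way.

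**3. CT against pathology, same model**

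P(truly lower | read high) = (1 − π)(1 − a) / [πa + (1 − π)(1 − a)]
- T: 0.0209/0.7328 = 3% to 0.1045/0.5 = 21%.
- N: 0.0267/0.6864 = 4% to 0.1335/0.5 = 27%.

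This is the gap that a baseline-CT-to-pathology shift would show in either arm without treatment. Randomisation balances it in expectation, so it drops out of a between-arm comparison.

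**4. What a between-arm comparison would deliver**
- Any binary stage category, 113 per arm: the 95% CI half-width is at most 1.96 × √(2 × 0.25/113) = 13 points.
- Regression grade at 44% against 8%: half-width 1.96 × √[(0.44 × 0.56 + 0.08 × 0.92)/113] = 10 points; power above 99.9% (two-sided 5%).
- With an 8% background, 80% power is reached at a NAC rate of about 21% (background 2%: about 11%; 15%: about 31%).

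**The case against.** **Condensed article.** It summarises a fuller protocol, and an analysis plan may exist, so a between-arm analysis could be specified elsewhere. That would answer mere silence. Here, however, the article assigns the measures by arm and draws a causal conclusion which that assignment does not support. That Ryan grading is confined to the NAC arm remains an inference from context.

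**Controls already show the CT error.** The planned control-arm comparison of baseline CT with pathology does estimate staging error. This stands, and it is why the remedy is cheap. But the article does not connect that estimate to the response analysis.

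Several stronger readings are tempting and are not supported:

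- *All response is measured against CT baseline.* The Ryan grade is a reading of the specimen and uses no CT baseline. The planned TNM change is CT against CT, so a patient over-staged on CT and lower at pathology is not, by this definition, a responder.
- *CT over-staging of 20–25% could produce all of the 20% downstaging quoted in the DISCUSSION.* The statement that "24% of control patients did not meet the criteria for AC" concerns the indication for adjuvant chemotherapy; stage II without adverse factors can also fail it. The 20.9% (1 − 0.791) mixes over- and under-staging. The quoted 20% is pathological downstaging to pT0-2N0M0, a different quantity. The same section also gives lower figures: 9.1% over-staging after NAC, and an ambiguously worded 7% for T2N0.
- *The response scales cannot be validated without untreated specimens.* Outcome by regression grade within the NAC arm is another route, and the article points to it when it cites recurrence of 30% without regression against 0% with complete response.
- *The trial cannot show that NAC induces response.* The stage data needed are collected in both arms; only the comparison is missing.

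**Conclusion.** The mismatch is real, and of moderate weight. As written, response is an uncontrolled within-arm estimate attached to a causal claim, and it overstates the NAC effect by an amount that the plan does not estimate.

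The size is only indicative. About 9 of 113 patients would be background responders if the cited 8% carried over to the modified Ryan scale, which the article does not establish. Apparent CT downstaging of 23–33% (T) or 29–39% (N) assumes independent reading errors and no true change, and would be smaller with correlated errors.

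A reader might infer that NAC has no effect on the tumour. That does not follow: an 8% background would not account for a rate near 44%. The size of the effect is in doubt, not its existence. The primary PFS comparison is unaffected.

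**What to change.** 1. In the sections on tumour response grade and on radiological–pathological correlation, add a randomised between-arm comparison of pathological T and N stage (ypT/ypN against pT/pN), stratified by the four CT strata used for randomisation (T3N−, T3N+, T4N−, T4N+). State how patients without a resection specimen are counted.
2. Base any statement that NAC induces response on that between-arm difference.
3. Keep CT TNM change, tumour volume, RECIST and the NAC-arm Ryan grade as descriptive results.
4. Where feasible, record the same regression grade on control specimens, preferably read without knowledge of arm, and report it as the background rate. Otherwise limit the abstract to describing regression grade within the NAC arm.

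**Cost.** The stage comparison needs no new data: baseline CT stage is fixed at randomisation and pathology is reported in both arms. Grading control specimens is a small addition to a specimen that is examined anyway. The downside is that the reported response may look less favourable.
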